## Summative impact evaluation

The summative impact evaluation has three research questions that will be examined during the 12-month follow-up period per participant. For evaluation purposes, the start of the intervention is operationalised as the point of randomization. The end is set as either the graduation from the programme (i.e., the point at which the delivery team and the programme participant jointly agree that the individual is no longer benefitting from the programme) or as dropping out from the programme due to, for example, imprisonment or death. Since it is unlikely that each individual will become a part of the programme immediately after being randomized into the treatment group, time from randomization to first contact by the delivery team is recorded in the process data and will be accounted for in the analysis.

The summative impact evaluation questions are as follows:

What is the difference in the number of violence against the person offences attributed to individuals receiving the focused deterrence intervention compared to those of similar individuals receiving business-as-usual support?What is the difference in the time to a violence against the person offence (in days) attributed to individuals receiving the intervention compared to those of similar individuals receiving business-as-usual support?What is the difference in the number of co-offending crimes (i.e., crimes involving two or more perpetrators) attributed to individuals receiving the intervention compared to those of similar individuals receiving business-as-usual support?

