### Outcome measures

The primary outcome for the impact evaluation is the number of violence against the person offences attributed to an individual within one year of randomisation. The secondary outcomes are:

the number of days between randomisation and a recorded violence against a person offence with a Police National Computer (PNC) disposal outcome relevant to the evaluation;when there is a co-offender, the number of recorded violence against the person offences attributed to an individual with a PNC disposal outcome relevant to the evaluation; andwhen there is a co-offender, the number of any recorded offences attributed to an individual with a PNC disposal outcome relevant to the evaluation.

For the purposes of this evaluation, PNC disposal outcomes relevant to the evaluation refer to all offences specified by the Home Office’s offence codes used in the court proceedings database as Violence Against the Person offences. Police-recorded violence against the person offences measure is the best outcome to evaluate the intervention’s effectiveness as it is a standard measure of violent behaviour [25]. Despite about half of all violent behaviour not being reported to the police, this rate decreases as the violence severity increases. Approximately 79% of violence against adults treated by a medical professional is captured, representing the most serious violent offending. However, reporting rates of violence against 10–15-year-olds are considerably lower, with less than 10% of all violence and 18% of violence resulting in medical treatment being reported [26].

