#### Multiple outcome testing

The study has a single primary outcome, as presented above. That will be the main result reported for the study and will not be adjusted for tests on secondary outcomes. We have secondary outcomes: (i) one on crime and (ii) two on co-offending. The study will adjust the co-offending analysis using the false-discovery rate [30]. All other analyses will be unadjusted. We know, *a priori*, that the study is not powered for sub-group analyses—any such analyses (along with anything not pre-specified) will be clearly labelled as exploratory.

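### As defined, the any-offence co-offending outcome admits only violence-coded disposals, so research question 3 is answered only for violent co-offending

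*Protocol article*

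**What the plan says.** **Research question.** The third question under Summative impact evaluation reads: "What is the difference in the number of co-offending crimes (i.e., crimes involving two or more perpetrators) attributed to individuals receiving the intervention", compared with similar individuals under business as usual. It is not limited to violence, whereas questions 1 and 2 both name violence against the person.

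**Outcomes.** Outcome measures lists two secondary outcomes that require a co-offender:

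- violent co-offending: "the number of recorded violence against the person offences attributed to an individual with a PNC disposal outcome relevant to the evaluation";
- any co-offending: "the number of any recorded offences attributed to an individual with a PNC disposal outcome relevant to the evaluation".

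The time-to-offence outcome carries the same disposal qualifier.

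**Definition.** The paragraph after the list says that "PNC disposal outcomes relevant to the evaluation refer to all offences specified by the Home Office’s offence codes used in the court proceedings database", and the sentence ends by naming violence against the person as the offence class. It applies to the whole evaluation and makes no exception for the any-offence outcome. No wider definition appears elsewhere in the article.

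**Multiplicity.** Multiple outcome testing states: "We have secondary outcomes: (i) one on crime and (ii) two on co-offending". It adds: "The study will adjust the co-offending analysis using the false-discovery rate".

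**The concern.** The two co-offending outcomes are meant to differ in the type of offence counted. The shared qualifier, once defined by violence codes, removes that difference: an offence of any type must still end in a violence-coded disposal to be counted.

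What is at stake is whether the trial can report on co-offending outside violence, which research question 3 includes. An analyst who follows the definition loses that information. An analyst who overrides it has to choose an offence list that the article does not fix, possibly after seeing data. In the first case, what is essentially one result would also be reported as two.

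**Working it through.** No sample size, power or alpha figure bears on this point, so there is no stated figure to reproduce. The check substitutes the definition into the two outcomes and then looks at the multiplicity step.

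**Step 1. Classify every co-offending record.** Use the two attributes in Outcome measures: whether the recorded offence is violence against the person (VAP), and whether the disposal is VAP-coded. A record counts in the violent outcome if both hold. It counts in the any-offence outcome if the disposal is VAP-coded. Research question 3 as worded counts every record.

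| Recorded offence | Disposal | Violent co-offending | Any co-offending | Research question 3 |
|---|---|---|---|---|
| VAP | VAP | 1 | 1 | 1 |
| VAP | not VAP | 0 | 0 | 1 |
| not VAP | VAP | 0 | 1 | 1 |
| not VAP | not VAP | 0 | 0 | 1 |

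**Step 2. Read the table.**

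- The two outcomes differ only in the third row, where an offence recorded as non-violent ends in a violence-coded disposal. If recorded offence and disposal share one classification, that row is empty and the counts are equal for every participant.
- The fourth row is ordinary non-violent co-offending. It counts in neither outcome, although research question 3 asks about it.

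**Step 3. Are these offences separate from violence in the article's own terms?** The Nottingham example under Eligibility criteria and recruitment lists robbery, drug offences, criminal damage and arson, weapon possession and public disorder alongside violence against the person, as separate items. This is one site's rule and refers to groups of three or more. It is used here only to show that the article treats the categories as distinct.

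**Step 4. Effect on the false-discovery adjustment.** The article gives one model specification for primary and secondary outcomes, so identical counts give identical p-values. I assume the Benjamini-Hochberg procedure. For two tests with p(1) ≤ p(2), the adjusted values are min(2 × p(1), p(2)) and p(2).

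- Identical outcomes, p = 0.03 and 0.03: min(0.06, 0.03) = 0.03, so both stay at 0.03.
- Identical outcomes, p = 0.049 and 0.049: min(0.098, 0.049) = 0.049, so both stay at 0.049.
- Distinct outcomes, p = 0.03 and 0.50: min(0.06, 0.50) = 0.06, so the pair becomes 0.06 and 0.50.

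The adjustment has work to do only when the two outcomes differ.

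**The case against.** **The intent is clear.** The list contrasts violence with offences of any type, and Multiple outcome testing counts two co-offending outcomes. The definition sentence is itself loosely worded, since it explains disposal outcomes as offences. This is probably a drafting slip, not a decision to discard non-violent co-offending. That stands, and it lowers the weight of the point. It does not remove it, because the only stated rule contradicts the outcome list and the research question.

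**The full protocol or the analysis plan may hold the code lists.** Neither is shown, so whether the collapse would occur in the actual analysis cannot be judged. But the point is not a missing detail. The article fixes a definition, and that definition conflicts with its own outcomes.

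**The outcomes need not be identical.** A reader might infer that two of the three secondary outcomes are the same variable with correlation 1. The documents do not support that without a condition. Recorded type and disposal code may disagree, and Outcome measures itself acknowledges inconsistencies in crime recording and outcome codes. Cases in the third row of the table would separate the counts.

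**The violent subset is what the trial cares about.** The formative evaluation section describes the summative focus as violent offending and group violence. If that is the intended scope, the any-offence outcome and the wording of research question 3 are too broad, and the passages still need reconciling.

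**The qualifier could attach to the individual.** Read as counting all co-offences among people who have a relevant disposal, the outcomes would differ. That reading selects people on an event after randomisation that the intervention is meant to change, and it still does not match research question 3.

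**Conclusion.** The point holds as a contradiction within the article. Read literally, the any-offence co-offending outcome collapses into the violent one, exactly under a single classification and nearly so otherwise. Non-violent co-offending is counted in neither.

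Three stronger conclusions might be drawn, and the documents do not carry them:

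- That research question 3 goes unanswered. It is answered for its violent subset.
- That the false-discovery step does harm. With coinciding outcomes it merely becomes redundant: no error rate is inflated and no power is lost.
- That eligibility across the trial rests on non-violent group offending. The list is given as Nottingham's example only.

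Two of the three secondary outcomes are involved. The amount of co-offending left out is unknown, because the article gives no share by offence type. The primary outcome, sample size and power are unaffected. The conclusion assumes that the qualifier applies to the offence and that no unshown document overrides the definition. It is worth correcting because the remedy is small and the gap concerns a question the trial sets itself.

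**What to change.** 1. Restrict the violence-code definition of a relevant disposal to the time-to-offence and violent co-offending outcomes.
2. State separately, before outcome data are seen, which offence codes and disposals count for the any-offence co-offending outcome, not limited to violence codes. The choice of list is for the trial team; the article gives no basis for naming one.
3. If only violent co-offending is intended, drop the third secondary outcome, narrow research question 3 to match, and remove the false-discovery adjustment, which would then have a single co-offending test.

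The cost is one or two sentences of text. Outcomes already come from each individual's PNC record, so the source is unchanged. Whether the extract and the data processing agreements with the police forces cover a wider code list is not shown and should be checked.

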### Analysis

Statistical significance tests will not be carried out to assess baseline balance, as their premise does not hold in randomised controlled trials (i.e., given that appropriate randomisation procedures were followed, any differences between control and treatment groups at baseline will be due to chance. See http://www.consort-statement.org/checklists/view/32-consort/510-baseline-data) [27]. Instead, tables of the pooled means (and standard deviations, where appropriate) for each characteristic and the magnitude of any differences explored will be presented. For skewed variables, quartile-based measures will be presented. In the statistical analysis plan, we will specify the details for assessing imbalance, which will set out criteria against variables used in randomisation and any putative time control variables used in our analysis to increase power (e.g., previous offending). We will also present balance visually—so, for previous offending, we will look at the distribution of offence counts by treatment and control.

#### Intention to treat analysis

Based on the project’s progress to date and our understanding of the proposed implementation, our analytical approach will pool individual data from all sites into a single analytical model. Our primary analysis will be based on intention-to-treat (ITT). That is, individuals will be analysed according to the group they are randomised to, regardless of whether they engaged with the intervention or remained in control. The ITT approach is particularly relevant for future policy-making stakeholders and practitioners who may roll out or implement a particular intervention without much control regarding how that intervention is taken up in the system. Therefore, the ITT approach allows for estimating the effects of offering that intervention and incorporates the imperfect uptake of that offer.

The statistical model for the ITT analysis is set out below in Eq 1. The model incorporates variables for between-site and over-time variation and variables used for stratification.
$$\text{Y}=\alpha +1\left[\text{treatment}\right]+2\left[\text{offending frequency}\right]+3\left[\text{adult}\right]+4\left[\text{site}\right]+5\left[\text{year/month}\right]+\epsilon$$(1)

In the equation, *Y* is the outcome—in this case, a count variable measuring the number of violent offences attributed to an individual in the twelve calendar months following the randomisation of an individual. The analysis approach will be based on count outcomes. We intend to use a *zero-inflated Poisson* (as reflected in our power simulations) because many individuals will likely not have further offences in the follow-up period of 12 months post-randomisation. 1[treatment] will be a binary variable where 0 = control and 1 = treatment, and the coefficient from this variable in the model will be the focal result for the project. 2[offending frequency] is one variable used for stratification in each site. We acknowledge that there is a difference between the model used in the power calculation and the analysis model presented here (S1 File). We will update the power calculations for our statistical analysis plan once we have sample data from sites to understand the likely outcome distribution (based on pre-intervention outcome data). This will be included in the analysis as n-1 dummy categories, with the reference category being the category with the largest number of observations from low, medium, or high offending frequency (note that not pre-specifying which category now will not affect the results). 3[adult] will be a binary variable for whether an individual is an adult (over 18) (= 1) or a child (under 18 years of age) (= 0). 4[site] will be site fixed effects—dummy variables for n-1 sites, again with the site with the largest number of observations overall as the reference category (anticipated to be either Coventry or Wolverhampton in the West Midlands). We include this variable because we know, *a priori*, that sites will differ in their eligibility criteria and selection processes. Hence, we need to account for between-site variation in our analysis. Finally, 5[year/month] will be a variable that captures the year and month since the start of the delivery period. This measure will capture seasonal variation and any esoteric shocks during delivery. This will be entered as a continuous variable, but if there are model convergence problems, we will aggregate this to year-quarter. We also acknowledge that it may be necessary to include another variable for offender sex, depending on the number of females included. If necessary, this would be a binary variable with 0 = male and 1 = female, determined by sex at birth, if possible, to determine this from available data.

For our analysis, we will use robust standard errors and calculate 95% confidence intervals based on those (the exact specification will be clarified in the statistical analysis plan). Standard error adjustment is sensible given that this helps in the event of model misspecification and heterogeneous treatment effects [28, 29]. The model specification will be the same for primary and secondary outcomes.

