#### Simulation

Based on this information, we created 10,000 simulated data sets with a similar distribution of the outcome for each of 32 combinations of effect size and sample size (see Table 2). Effect size was simulated by artificially manipulating the outcome for the treatment group and this was modelled using a negative binomial regression analysis. For each combination of effect size and sample size, the proportion of the 10,000 estimates of treatment effect that were statistically significant was stored and is visualised in Fig 1. Reproducible code for these analyses is included as a S1 File.

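### The focal result is one coefficient of a zero-inflated Poisson model, which equals the intention-to-treat ratio of mean offences only if treatment leaves the structural-zero share unchanged

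*Protocol article*

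**What the plan says.** Under Outcome measures, the primary outcome is "the number of violence against the person offences attributed to an individual within one year of randomisation". The first question under Summative impact evaluation asks for the difference in that number between arms. The section on intention-to-treat analysis explains the choice of ITT: "the ITT approach allows for estimating the effects of offering that intervention and incorporates the imperfect uptake of that offer".

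The same section names a zero-inflated Poisson, giving the expected number of people without further offences as the reason. It says of the treatment indicator that "the coefficient from this variable in the model will be the focal result for the project". Eq 1 shows one linear predictor with one treatment term. Nothing states what enters the zero-inflation part, or that arm means will be derived from the fit.

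On power, the section describes the ZIP as "as reflected in our power simulations) because many individuals will likely not have further offences in the follow-up period of 12 months post-randomisation". The Simulation subsection says of the simulated outcome that "this was modelled using a negative binomial regression analysis", and the Data subsection calls the observed distribution negative binomial. A few sentences after the ZIP remark the article adds: "We acknowledge that there is a difference between the model used in the power calculation and the analysis model presented here (S1 File". It promises updated power in the statistical analysis plan.

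On robust errors it says: "Standard error adjustment is sensible given that this helps in the event of model misspecification".

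**The concern.** A ZIP treats each count as coming either from a latent class that is always zero (share π) or from a Poisson class with rate λ. Its count coefficient b describes λ only. The question asked is about the mean over everyone randomised, which depends on both π and λ.

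The gap matters in this trial. The Introduction lists extra opportunities to desist among the three components of the intervention, and the mechanism table (Table 3) names pathways to desistance. The interim harm and roll-out limits are set on reoffending prevalence, that is, on the split between zero and non-zero counts. An effect on the zeros is therefore one of the effects the programme seeks, and a coefficient on λ alone can miss or dilute it. The trial's main number could then understate a real fall in offences.

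**Working it through.** **Inputs from the article.** N about 1,700, allocated 1:1, so 850 per arm. A 26% relative reduction is said to be detectable in 80% of trials, so the target ratio is 1 − 0.26 = 0.74. Table 2 gives power 0.6461 at n = 1700 and ratio 0.8, and 1 at ratio 0.7.

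**Assumptions.** Two-sided 5% level, in line with the 95% intervals. The article gives no outcome mean, dispersion or structural-zero share, so these are varied.

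**Step 1: the plan's own figure.** The 26%/80% statement cannot be rebuilt without the negative binomial parameters, so it was compared with Table 2.
- Linear interpolation at ratio 0.74: 0.6461 + 0.6 × (1 − 0.6461) = 0.858. The 80% point is 20% + 10% × (0.80 − 0.6461)/(1 − 0.6461) = 24.3%.
- Normal approximation, power = Φ(c√n·|ln RR| − 1.96), with c = 0.2538 from the 0.6461 cell: Φ(0.2538 × 41.23 × 0.3011 − 1.96) = Φ(1.19) = 0.88. The 80% point is 23.5%.
- The columns of Table 2 imply different c (about 0.25, 0.41 and 0.34 for ratios 0.8, 0.7 and 0.6), so the stated figure is neither confirmed nor refuted. It belongs to a negative binomial analysis in any case.

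**Step 2: what the coefficient estimates.** With arm mean (1−π)λ,

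ratio of arm means = [(1−π₁)/(1−π₀)] × exp(b).

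So exp(b) is the ITT ratio only when π₁ = π₀. Example with π₀ = 0.5, λ₀ = 1.5 (control mean 0.75):
- Desistance only: 1−π₁ = 0.5 × 0.74 = 0.37 and λ₁ = 1.5. The treated mean is 0.555 and the ratio 0.74, but exp(b) = 1.
- More desistance with a higher rate among the rest: 1−π₁ = 0.5 × 0.64 = 0.32 and λ₁ = 1.5 × 0.74/0.64 = 1.734. The ratio is again 0.74, but exp(b) = 1.16.

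**Step 3: size by simulation.** 850 per arm, true ratio of means 0.74, robust standard errors, no covariates. Cells show the median estimate, then the share of trials rejecting.

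| Data and effect | ZIP, treatment in both parts | ZIP, constant inflation | Ratio of arm means |
|---|---|---|---|
| ZIP data (π₀/λ₀ 0.5/1.5, 0.6/1.0, 0.4/2.0), desistance only | 0.99–1.00; 5.0–5.7% | 0.81–0.90; 42–53% | 0.74; 81–99.7% |
| Same, rate only | 0.73–0.74; 61–99.8% | 0.73–0.74; 88–99.9% | 0.73–0.74; 87–99.8% |
| Negative binomial, mean 0.5–1, dispersion 1–2, 26% of treated set to zero | about 0.99; 5–7% | 0.78–0.91; 17–73% | 0.73–0.75; 77–93% |
| Negative binomial, mean 0.5–1.5, dispersion 2–3, uniform reduction | 0.77–0.80; 43–77% | 0.75–0.79; 70–85% | 0.73–0.74; 83–94% |

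With mean 0.5–1 and dispersion 1–2, constant inflation under a uniform reduction gives 0.75–0.77 with power 77–87%. In the mixed case of Step 2, on the three ZIP data sets, the both-parts coefficient is 1.16 and significant in the harmful direction in 23–74% of trials, while the ratio of means stays at 0.74. With no effect (negative binomial, mean 0.75, dispersion 2) all three methods reject in about 5% of trials. The problem is the target and the power, not false positives.

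**Step 4: the power remark.** The Simulation subsection names negative binomial regression. The ITT section first says the ZIP was reflected in the simulations and then says the two models differ. The first statement conflicts with the other two.

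**The case against.** Four points on the other side deserve weight.

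1. **One predictor, one coefficient.** Eq 1 is most simply read as treatment in the count part with constant inflation. Then (1−π) cancels and, under that model, exp(b) is the ratio of arm means. A reader might infer that the coefficient can never be the ITT effect; the article does not support that. What stands is that this reading assumes no effect on structural zeros, and the estimate is diluted when there is one.

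2. **The striking figures are conditional.** Detection at 5% needs treatment in both parts and an effect made up only of desistance. The article specifies neither, and the Introduction describes several mechanisms. It would be wrong to infer that this trial has 5% power. Under the simplest reading and a uniform reduction the loss is modest.

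3. **The Poisson part is not shown to be wrong.** The negative binomial description concerns pre-intervention offences without conditioning on covariates, and a ZIP is itself overdispersed overall. What stands is that many zeros alone do not call for zero inflation, since a negative binomial also produces them. Robust standard errors correct the variance of the estimate, not what the coefficient estimates.

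4. **The power mismatch is disclosed.** The article admits the difference and promises an update, so this is a wording error, not a concealed mismatch.

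The analysis plan may define the zero part or a marginal contrast. The concern does not rest on that gap: the article already commits to the coefficient as the focal result.

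**Conclusion.** The concern holds in a conditional form. The chosen coefficient answers the trial's question only if treatment leaves the structural-zero share unchanged, which sits badly with a programme that aims at desistance. That follows from algebra and needs no assumed rates.

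The size depends on the unstated specification:
- **Treatment in both parts:** a pure desistance effect worth 26% of mean offences goes undetected beyond chance, at about 5%.
- **Constant inflation:** a uniform reduction is nearly recovered, but desistance shrinks to about 0.78–0.91 with power 17–73%, against 77–93% for the ratio of means.

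These ranges rest on assumed means of 0.5–1 and dispersions of 1–2, without the Eq 1 covariates. They illustrate the effect and do not forecast this trial's loss. Separately, the statement that the simulations reflect the ZIP is wrong on the article's own account, so the 26%/80% figure was not derived for the focal coefficient.

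**What to change.** - Define the focal effect as the ratio, and the difference, of mean one-year offence counts by randomised arm.
- Estimate it by negative binomial or Poisson log-link regression with robust standard errors and the Eq 1 covariates. If the ZIP is kept, put treatment in both parts, standardise to marginal means by arm, and report that contrast instead of the count coefficient.
- Delete the parenthesis saying that the ZIP is reflected in the power simulations.
- Base the promised power update on the final model and contrast.

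The cost is wording in the protocol and analysis plan plus the power run already promised. No data collection changes, and the log-link mean model is simpler to fit than the ZIP.

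### The count-model specification is extended to every secondary outcome, including days to a violent offence, which is a censored time that a zero-inflated count model does not fit

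*Protocol article*

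**What the plan says.** Under Intention to treat analysis, Eq 1 sets out the covariates: treatment, offending frequency, adult status, site and calendar time. The text then says "The analysis approach will be based on count outcomes" and gives the model family: "We intend to use a *zero-inflated Poisson* (as reflected in our power simulations) because many individuals will likely not have further offences in the follow-up". The section ends with "The model specification will be the same for primary and secondary outcomes", and no outcome is excepted. In that closing paragraph only the exact form of the robust standard errors and confidence intervals is left to the statistical analysis plan.

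Multiple outcome testing lists the outcomes that the rule covers: "We have secondary outcomes: (i) one on crime and (ii) two on co-offending". Outcome measures defines the first of them as "the number of days between randomisation and a recorded violence against a person offence" with a relevant disposal. It answers the second research question under Summative impact evaluation, which asks about time to a violent offence in days. That section says the questions are "examined during the 12-month follow-up period per participant". It also foresees participants "dropping out from the programme due to, for example, imprisonment or death".

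**The concern.** The feature that motivates the zero-inflated model for the primary outcome makes the model unsuitable for this one. A participant with no offence in 12 months has a true count of zero. The same participant has no observed time to offence; all that is known is that the time exceeds 12 months. A value of zero days would mean offending at once, the opposite of what happened.

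Taken at its word, the closing sentence sends this outcome to a count model, so non-offenders must be dropped or given a number. Dropping them conditions on reoffending, which happens after randomisation, and so abandons the intention-to-treat comparison that the section adopts. Giving them a number makes the answer depend on which number. What is at stake is the pre-specified answer to one of the three summative research questions: its size, and under one coding its direction, would rest on a choice that could be made after the data are seen.

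**Working it through.** The plan states no figure for this outcome, so there is none to reproduce. The check asks what the stated rule would deliver under each way of handling non-offenders.

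**Inputs from the article.** N about 1,700 and 1:1 allocation, so 850 per arm; 12-month follow-up; robust standard errors.

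**Assumptions, not in the article.** Control 12-month reoffending p0 of 20%, 30% or 50%; constant hazards; hazard ratio (HR) 0.74, borrowed from the article's 26% detectable reduction, which refers to offence counts and not to hazards.

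**Set-up.** With time in years, L0 = −ln(1 − p0), L1 = 0.74 × L0 and p1 = 1 − exp(−L1). At p0 = 30%, L0 = 0.3567, L1 = 0.2639 and p1 = 0.232. Events are 850 × 0.30 = 255 and 850 × 0.232 = 197, together 452.

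**(A) Non-offenders dropped.** Mean time among offenders is 365 × [1/L − exp(−L)/(1 − exp(−L))].
- Control 171.7 days, treated 174.5 days, SD about 105.
- Difference 2.8 days; SE = 105 × √(1/255 + 1/197) ≈ 10.0; z ≈ 0.28; power about 6%.

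A zero-inflated Poisson with non-offenders entered as zeros comes to much the same in its count part. A Poisson variable with mean near 170 is almost never zero, so every zero goes to the inflation part and the count part compares reoffenders only.

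**(B) Non-offenders coded 0, overall mean compared.** The mean is p × the value in (A): 0.30 × 171.7 = 51.5 days against 0.232 × 174.5 = 40.5 days, a ratio of 0.79. A treatment that prevents offences appears to bring them forward.

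**(C) Non-offenders coded 365.** This is the restricted mean offence-free time, 365 × (1 − exp(−L))/L: control 307.0 days, treated 320.8 days, ratio 1.045. With the variance from E[X²] = 2∫t·exp(−Lt)dt over 0 to 1 year, the SE of the 13.8-day difference is about 4.9 days; z ≈ 2.83; power about 81%.

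**(D) Cox regression.** By Schoenfeld's formula, z = |ln 0.74| × √452 / 2 = 0.301 × 21.26 / 2 = 3.20, and power = Φ(3.20 − 1.96) ≈ 89%.

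**Simulation over the range.** 300 data sets per scenario, censoring at 365 days, treatment as the only covariate; robust Poisson for A to C, Cox for D; true HR 0.74. The Monte Carlo error is about 1 to 3 percentage points on each rate.

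| Handling | Mean estimate at p0 = 20/30/50% | Rejection rate |
|---|---|---|
| A. Dropped | ratio of mean days 1.01/1.02/1.03 | 3/5/15% |
| B. Coded 0 | ratio of mean days 0.77/0.79/0.83 | 58/65/80%, wrong direction |
| C. Coded 365 | ratio of mean days 1.03/1.04/1.09 | 63/79/98% |
| D. Cox | HR 0.743/0.749/0.736 | 76/88/99% |

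Schoenfeld power for D is 74/89/99%, on 299, 452 and 766 events. With HR = 1, rejection was about 3 to 8% under every handling.

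**The case against.** The best defence is that model specification means only the right-hand side of Eq 1 and the robust standard errors. Eq 1 has a generic Y and names no distribution. The count form is introduced for the outcome then under discussion, the zero-inflated Poisson is worded as an intention, and the sentence closes a paragraph on standard errors. This reading is possible. The article does not state it, however, and describes the analysis approach as count-based. If it is what was meant, the sentence still needs to say so.

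A second defence is that censoring rules and coding belong in the analysis plan, which is not shown. That stands for the detail: their absence is not a fault of the article. It does not cover a sentence that fixes the model rule for all secondary outcomes.

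A reader might go further and infer that no count-type analysis of days could answer the question. That is too strong. Coding non-offenders 365 gives a restricted mean time, an intention-to-treat quantity that does not need proportional hazards, and robust standard errors make its comparison sound if follow-up is complete. But it has no zeros, so it is not a zero-inflated analysis, and the plan does not state it.

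A reader might also infer false-positive findings. In one simulated data set, a zero-inflated Poisson gave a count coefficient of −0.047 with a model-based SE of 0.007. The article requires robust errors. With SD/mean of about 105/172 and about 298 and 207 offenders, the SE is about 0.61 × √(1/298 + 1/207) ≈ 0.055, so z is about 0.86 and the result is not significant.

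**Conclusion.** The point holds in a limited form. As worded, the article applies a count specification, with an intended zero-inflated Poisson, to a right-censored time. The consequences are a wrong target quantity, lost power or a reversed direction, depending on an unstated coding. At an assumed 30% control prevalence and HR 0.74, simulated rejection runs from about 5% with reoffenders only, through 79% for a restricted mean, to 88% for Cox. These figures illustrate the size; prevalence, constant hazards and HR are assumptions.

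The documents do not support a larger claim. One of three secondary outcomes is affected. The primary analysis is untouched, the co-offending counts suit a count model, and type I error is not grossly inflated with robust standard errors. It should be fixed before analysis, but it does not threaten the trial's main result.

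**What to change.** Restrict the closing sentence of Intention to treat analysis to the count outcomes, or state that it refers only to the Eq 1 covariates and the robust standard errors.

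For days to first violent offence, name an intention-to-treat time-to-event analysis with randomisation as time zero, censoring at 12 months and the Eq 1 covariates. Cox regression is one valid choice. A difference in restricted mean time is another, and may be preferable if delay between randomisation and first contact makes hazards non-proportional. State how death and imprisonment, both foreseen in the article, are handled statistically (as censoring or as competing events), and show Kaplan-Meier or cumulative incidence curves.

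The cost is a sentence or two in the protocol and the matching text in the analysis plan. Offence and randomisation dates are already to be collected, so no new data are needed for the time variable.
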